## 1. Background

Chronic kidney disease (CKD) represents a significant and escalating global public health challenge, with a particularly heavy burden in China that affects approximately 120 million individuals, the majority of whom are in the early stages (1-3) where intervention is most effective. However, despite this high prevalence, CKD remains substantially underdiagnosed and inadequately managed in primary care settings where most patients initially present. This considerable care gap persists even though primary care physicians (PCPs) serve as the frontline managers, a situation compounded by critically low public disease awareness (12.5%)—largely due to the disease’s insidious onset—and insufficient knowledge among PCPs themselves, as evidenced by only 24.9% awareness rate of fundamental CKD concepts, staging, and management principles among those in Beijing. This dual deficit in awareness creates a significant imbalance between the existing healthcare supply capabilities and the population's needs for effective CKD prevention and management.

Digital tools for CKD management in primary care have evolved from basic eGFR reporting to comprehensive clinical decision support systems (CDSS). While the introduction of eGFR reporting improved renal referral rates, it showed limited impact on key process measures like renin-angiotensin-aldosterone system inhibitors (RAASi) use. Subsequent generations of CDSS, incorporating educational modules and multifactorial interventions, have yielded only modest or inconsistent improvements in care processes and patient outcomes in high-income countries. This limited effectiveness may be attributable to the already high baseline standard of CKD management in these settings, thereby constraining the potential for substantial further gains. In contrast, the considerable CKD burden, suboptimal management in primary care, and constrained specialist nephrology resources in China provide an ideal environment for CDSS implementation to enhance care quality. Despite this potential, no prior trials have evaluated the effectiveness of such interventions in Chinese primary care system.

This study is designed to address these gaps by developing a CKD-specific CDSS, contextualized for China's primary care setting through a multidisciplinary team that includes PCPs, nephrologists, and other specialists. A subsequent multicenter cluster-randomized trial will be conducted to evaluate the effectiveness of this CDSS versus usual care on both process measures and clinical outcomes. The CDSS will provide comprehensive support, encompassing screening, diagnosis, and management guidance. To isolate the effect of CDSS from that of general CKD training, government-supported CKD training will be provided to both study arms. This innovative approach aims to validate a scalable model for early CKD prevention and

---

control in Chinese communities, thereby ultimately generating evidence-based support to alleviate the CKD disease burden.

## **2. Research Hypothesis and Research Objectives**

### **2.1 Research Hypothesis**

Our central hypothesis is that the implementation of a tailored CDSS will optimize PCPs' medical behaviors—including screening, diagnosis, and treatment—which will, in turn, lead to improved patients' outcomes and a consequent reduction in the burden of CKD in the community setting.

### **2.2 Research Objectives**

#### **2.2.1 Primary Objectives**

1. To assess the effect of the CDSS on the composite endpoint of kidney-related and cardiovascular hospitalization rates among community CKD patients.
2. To evaluate the impact of CDSS on kidney-related hospitalization rate among community patients at high risk for CKD.

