### 3. Research Design

This study employs a multicenter, parallel-group, cluster-randomized controlled trial design. A total of 30 community health centers in the Xicheng District of Beijing will be recruited, with each center constituting a cluster. The study population consist of adult CKD patients and patients at high-risk for CKD-who are regularly managed at these centers, defined as having two or more visits documented in the Electronic Health Record (EHR) system during a designated 12-month screening period. Baseline characteristics, including CKD diagnosis (based on ICD codes) and clinical measures (e.g., the most recent blood pressure, HbA1c, and LDL-c values), were all ascertained from data recorded during this screening period. These 30 clusters will be stratified by their annual patient visit volume (large, medium, small) and subsequently randomized in a 1:1 ratio to either the intervention or control group. Following randomization and prior to the formal initiation of the intervention, both groups will receive the government-supported structured training. The intervention group will then implement a CKD-specific CDSS integrated into their existing EHR platforms, in addition to providing government-supported structured training. The control group will continue with usual care, also supplemented by the same government-supported training to isolate the effect of the CDSS itself. The trial will employ a two-phase evaluation scheme: a 6-month initial phase assessing the impact of the CDSS on process measures (CKD diagnosis, RAASi/SGLT-2i use) and short-term clinical control rates (blood pressure, HbA1c, LDL-c), and the final 36-month phase evaluating its effects on the primary composite endpoint of kidney and cardiovascular hospitalization rates, alongside a comprehensive health economic analysis, which will be conducted through linkage with the centralized Beijing Health Insurance Database.

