## **3.3 Study Outcomes**

### **3.3.1 Main Outcomes**

1. Hospitalization rates for kidney-related (acute kidney injury, progression of kidney disease, or requiring dialysis) or cardiovascular events including myocardial infarction, stroke, heart failure, or cardiovascular procedures) among CKD patients.

2. Hospitalization rates for kidney-related events in patients at high-risk for CKD

Data sources for main outcomes: Electronic medical record systems of community medical institutions and Beijing medical insurance claims database.

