### **3.4.4 Study Duration and Phases**

The 36-month intervention period are divided into two phases: (1) an initial six-month evaluation (Phase 1) for process measures and short-term clinical outcomes, and (2) a three-year evaluation (Phase 2) for long-term outcomes, with a composite of kidney and cardiovascular hospitalization rates as the primary endpoint.

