## **3.6 Statistical Analysis**

### **3.6.1 Sample Size and Statistical Power**

The primary outcome is a composite hospitalization rate for kidney-related (acute kidney injury, progression of kidney disease, or requiring dialysis) or cardiovascular events (myocardial infarction, stroke, heart failure, or cardiovascular procedures). Based on data from the US CRIC cohort, the all-cause hospitalization rate for CKD patients is 35.0 per 100 person-years. The sample size calculation aims to detect a 20% reduction in this rate following 36 months of CDSS intervention, compared to usual care. The calculation is performed using cluster randomization tools (online calculator at <https://clustercts.shinyapps.io/rshinyapp/>) with the following parameters: 30 randomized centers (15 per arm), an intraclass correlation coefficient of 0.02, and a significance level of 0.05. A total sample size of 3,240 participants is estimated to provide 90% statistical power (**Figure 1**).

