### **3.6.2 Data Analysis**

#### **3.6.2.1 Analysis Principles**

Categorical variables will be described as frequencies and percentages. Continuous variables will be summarized as means with standard deviations or as medians with interquartile ranges, based on their distribution. The primary outcome of hospitalization rate will be analyzed using generalized linear mixed models (GLMMs). Both unadjusted and adjusted estimates will be presented; adjusted analyses will include age, sex, comorbidities (including diabetes, hypertension, and cardiovascular disease), and baseline eGFR. Other secondary outcomes will be analyzed using the same approach but without adjustment for baseline eGFR.

For missing data, if the proportion of missingness is below 20%, continuous variables will be imputed using regression-based methods and categorical variables using predictive mean matching. Any variable with over 20% missing values will be excluded from the analysis.

All analyses will adhere to the intention-to-treat (ITT) principle. Given the pragmatic trial setting, a decline in adherence is anticipated. Should adherence to the CDSS intervention fall below 60%, a secondary as-treated (AT) analysis will be performed as pre-specified. All statistical analyses will be conducted using RStudio (v2022.02.03).

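### The protocol lists two primary outcomes in two populations in some sections and one in others, and never says which result counts as primary success

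*Protocol*

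**What the plan says.** Two places in the protocol put two outcomes on the same level.

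- Section 2.2.1, Primary Objectives, item 1: "To assess the effect of the CDSS on the composite endpoint of kidney-related and cardiovascular hospitalization rates among community CKD patients". Item 2: "To evaluate the impact of CDSS on kidney-related hospitalization rate among community patients at high risk for CKD".
- Section 3.3.1, Main Outcomes, repeats the pair. Its second item is "Hospitalization rates for kidney-related events in patients at high-risk for CKD". This outcome appears in neither secondary list (2.2.2 and 3.3.2).

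Other places recognise only the composite.

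- Section 3, Research Design, says that the 36-month phase evaluates "its effects on the primary composite endpoint of kidney and cardiovascular hospitalization rates".
- Section 3.4.4 describes the three-year evaluation "with a composite of kidney and cardiovascular hospitalization rates as the primary endpoint".
- Section 3.5.1 uses the term study endpoint for the composite in CKD patients alone.
- Section 3.6.1 opens with "The primary outcome is a composite hospitalization rate for kidney-related" and cardiovascular events, takes a hospitalisation rate for CKD patients, and uses "an intraclass correlation coefficient of 0.02, and a significance level of 0.05".
- Section 3.6.2.2 defines the primary endpoint read at three years as the composite.

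Section 3.1.1 also makes CKD patients the main focus and describes the high-risk cohort as something the analysis will include.

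**The concern.** The number of primary outcomes is a protocol-level decision, and this protocol gives two answers. As long as both stand, the choice of which result meets a primary objective could be made after the results are known. A trial that missed on the CKD composite but reached significance in high-risk patients could cite 2.2.1 and 3.3.1. A trial with the opposite pattern could cite 3.4.4 and 3.6.1.

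The label also governs parts of the planned analysis. Section 3.6.2.1 adjusts the primary outcome for baseline eGFR but analyses secondary outcomes without it, so the covariates for the high-risk outcome depend on an unsettled classification. Section 3.6.2.2 fixes a three-year reading for the composite and 6- and 12-month readings for secondary endpoints. It does not say when the high-risk hospitalisation outcome is read.

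If the second outcome really is primary, it has no design basis: no event rate, target effect, cohort size or power is given for it.

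**Working it through.** **Inputs from section 3.6.1.** 30 centres (15 per arm), 3,240 patients (3,240/30 = 108 per centre), ICC 0.02, significance level 0.05 (sidedness not stated; two-sided assumed), control rate 35.0 per 100 person-years, 20% reduction (to 28.0), 36 months, stated power 90%.

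**Step 1: the plan's own figure.** Design effect = 1 + (108 − 1) × 0.02 = 3.14. Effective sample size per arm = 1,620/3.14 = 515.9.

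- Three-year event counts with Poisson variance, 1.05 v 0.84 per patient: SE = √((1.05 + 0.84)/515.9) = 0.0605, and 0.21/0.0605 = 3.47. Power is 0.934 by the normal approximation and 0.917 with t on 28 df.
- Three-year risks, 1 − 0.65³ = 0.725 v 1 − 0.72³ = 0.627: power is 0.926 (normal) and 0.907 (t).

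The stated 90% is thus roughly reproduced on these 36-month readings with t. The sample size is not matched exactly: solving for 90% gives 2,670 and 3,000. Other readings fall short; 35% v 28% as simple proportions gives 0.649 with t. On every reading the calculation concerns CKD patients and one test at 0.05. Nothing in it bears on the high-risk outcome.

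**Step 2: familywise error under each reading of the protocol.**

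| Reading | Chance of a false primary claim |
|---|---|
| Composite alone is primary | 0.05 |
| Both primary, both must succeed | at most 0.05 |
| Both primary at 0.05, either suffices, independent | 1 − 0.95² = 0.0975 |
| Same, correlation 0.2 | 0.096 |
| Same, correlation 0.5 | 0.091 |
| Same, correlation 0.8 | 0.078 |

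The correlated values come from a bivariate normal with two-sided tests. The patients differ but the centres and their allocation are shared, so some positive correlation is plausible. The bound under any dependence is 0.05 + 0.05 = 0.10.

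**Step 3: power for the second outcome.** This cannot be computed from the protocol. For illustration only, assume a kidney hospitalisation rate of 0.2 to 5 per 100 person-years, a 20% reduction, the same ICC of 0.02, 108 to 1,000 high-risk patients per centre, and three years. Power then runs from about 4% to 32% (t on 28 df, counting only the favourable tail). Under a both-must-succeed rule, overall power could not exceed these values.

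**Step 4: what an equal alpha split would cost the composite.** At 0.025 each, the familywise error is 1 − 0.975² = 0.0494 if independent. With 3,240 patients, power for the composite falls from 0.917 to 0.858 (counts, t) or from 0.907 to 0.843 (risks, t). Restoring 90% would take about 5,190 or 6,240 patients in the same 30 centres.

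**The case against.** The strongest reply is that the protocol already gives the composite precedence in substance. The sections on design, phases, sample size and timing of analysis all treat it as the only primary endpoint, 3.5.1 calls it the study endpoint, and 3.1.1 puts CKD patients first. On this view 2.2.1 and 3.3.1 are loosely labelled, and no second primary test was ever planned. That carries weight, and it is the reason for resolving the conflict in favour of the composite. It does not remove the conflict, because a numbered primary objective repeated as a main outcome and absent from both secondary lists is more than a stray label.

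A reader might infer that the trial runs a 9.75% type I error. The documents do not support that. The figure requires that both outcomes are primary, that each is tested at 0.05, and that either suffices. The only 0.05 in the protocol is an input to the composite's sample size, and no rule of success is stated. Whether claims in two separate populations need joint error control is also partly a matter of judgement; each claim alone would still carry 5%.

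A reader might also infer that the absence of an alpha split or hierarchy is itself a fault. A multiplicity procedure is commonly left to the statistical analysis plan, which is not available here. What an analysis plan cannot properly settle is how many primary outcomes the protocol has.

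**Conclusion.** The contradiction is established from the protocol's own text: two primary objectives and main outcomes in 2.2.1 and 3.3.1, and one primary endpoint in 3, 3.4.4, 3.6.1 and 3.6.2.2. Only the composite is powered.

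The effect on error is conditional. It is 9.75% with independent tests, or about 9.1% at correlation 0.5, if both outcomes are primary at 0.05 with either sufficient. It is nil if the composite alone is primary or if both must succeed. These figures assume two-sided tests. Since the protocol does not choose between the readings, the firm conclusion is that the primary claim is not fixed in advance. Every reading requires an edit: the composite-only reading needs 2.2.1 and 3.3.1 changed, and either two-primary reading needs a stated rule and a power basis for the second outcome.

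**What to change.** Amend 2.2.1 and 3.3.1 so that kidney/cardiovascular hospitalisation in CKD patients is the single primary outcome, in line with 3, 3.1.1, 3.4.4, 3.5.1, 3.6.1 and 3.6.2.2. List kidney-related hospitalisation in high-risk patients as a key secondary outcome. It could, for example, be tested at 0.05 only if the composite is significant. In the same amendment, state its time of analysis and its covariates, because 3.6.2.1 and 3.6.2.2 treat primary and secondary outcomes differently.

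This keeps the full 0.05 and the stated sample size for the composite. The cost is a protocol amendment that lowers the status of a numbered objective in a study that already has ethics approval, so it is more than an editorial change. With the sequential test, a real benefit in high-risk patients could not be confirmed if the composite fails.

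If the sponsor wants two primary outcomes, the protocol should instead state the alpha split or the both-must-succeed rule, give an event rate and power for the high-risk outcome, and restate power for the composite. Either change should be made before any hospitalisation results are seen by arm.

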#### **2.2.2 Secondary Objectives**

##### **Process Measures:**

1. To assess the effect of the CDSS on the underdiagnosis of CKD, as measured by the rate of appropriate ICD-coded documentation in patient records.
2. To examine the change in the utilization rates of renoprotective medications (RAASi and sodium-dependent glucose transporters 2 inhibitor [SGLT2i]) among CKD patients.
3. To evaluate the impact of the CDSS on the screening rate for CKD (SCr and/or urine protein testing) among patients at high risk for CKD.
4. To determine the effect of the CDSS on the referral rate of CKD patients who meet guideline-based criteria for nephrology consultation.

##### **Clinical Outcome Measures:**

5. To evaluate the effect of the CDSS on blood pressure control (target: <130/80 mmHg) among patients with CKD.
6. To assess the impact of the CDSS on glycemic control (target: HbA1c <7%) among patients with diabetic kidney disease.
7. To examine the effect of the CDSS on lipid management (target: LDL-C <2.6 mmol/L) among patients with CKD.

##### **Health Economic and Implementation Outcomes:**

8. To analyze the cost-effectiveness of the CKD screening and management program within the community setting.
9. To conduct a comprehensive process evaluation of CDSS implementation using the RE-AIM framework.

---

### 3. Research Design

This study employs a multicenter, parallel-group, cluster-randomized controlled trial design. A total of 30 community health centers in the Xicheng District of Beijing will be recruited, with each center constituting a cluster. The study population consist of adult CKD patients and patients at high-risk for CKD-who are regularly managed at these centers, defined as having two or more visits documented in the Electronic Health Record (EHR) system during a designated 12-month screening period. Baseline characteristics, including CKD diagnosis (based on ICD codes) and clinical measures (e.g., the most recent blood pressure, HbA1c, and LDL-c values), were all ascertained from data recorded during this screening period. These 30 clusters will be stratified by their annual patient visit volume (large, medium, small) and subsequently randomized in a 1:1 ratio to either the intervention or control group. Following randomization and prior to the formal initiation of the intervention, both groups will receive the government-supported structured training. The intervention group will then implement a CKD-specific CDSS integrated into their existing EHR platforms, in addition to providing government-supported structured training. The control group will continue with usual care, also supplemented by the same government-supported training to isolate the effect of the CDSS itself. The trial will employ a two-phase evaluation scheme: a 6-month initial phase assessing the impact of the CDSS on process measures (CKD diagnosis, RAASi/SGLT-2i use) and short-term clinical control rates (blood pressure, HbA1c, LDL-c), and the final 36-month phase evaluating its effects on the primary composite endpoint of kidney and cardiovascular hospitalization rates, alongside a comprehensive health economic analysis, which will be conducted through linkage with the centralized Beijing Health Insurance Database.

#### 3.1 Research Subjects

##### 3.1.1 Study Population

The study population comprise adult patients managed across 30 community health centers in Xicheng District, Beijing (**Table 1**). To ensure sufficient data for follow-up, patients were selected from all visits to these centers during a one-year screening period (March, 10, 2022 – March, 10, 2023), with the inclusion criterion of having at least two visits during this period. The study is primarily focused on CKD patients, while analysis will include a cohort of high-risk population for developing CKD. ICD codes for defining diseases in study population inclusion/exclusion criteria are summarized in **Table 2**.

##### 3.1.2 CKD Patients

###### 3.1.2.1 Inclusion Criteria

1. Age $\geq$ 18 years

- 
2. Diagnosis of CKD, defined as meeting at least one of the following criteria:
- (1) Two estimated glomerular filtration rate (eGFR) values  $<60 \text{ mL/min/1.73m}^2$  (calculated using the CKD-EPI equation), obtained  $\geq 90$  days apart.
  - (2) Confirmed proteinuria, defined as two positive results  $\geq 90$  days apart for either urine albumin-to-creatinine ratio (UACR)  $\geq 30 \text{ mg/g}$ , urine dipstick  $\geq 1+$ , or 24-hour urine total protein (UTP)  $\geq 150 \text{ mg}$ .
  - (3) Documented CKD diagnostic codes in the EHR, supplemented by at least one qualifying eGFR or proteinuria result meeting the above thresholds.

3. Beijing medical insurance residents.

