### **3.3.2 Secondary Outcomes**

- 
1. Changes in CKD diagnosis rate: the difference in the proportion of CKD patients with an ICD-code for CKD documentation between the follow-up and baseline periods.
  2. Changes in utilization of renoprotective medications: the difference in prescription rates of RAASi and SGLT2i among CKD patients between the follow-up and baseline periods, reported separately.
  3. Changes in screening rate for CKD: the difference in the proportion of patients at high risk for CKD who complete SCr and/or urine protein testing between the follow-up and baseline periods.
  4. Changes in renal referral rate: the difference in the proportion of CKD patients meeting criteria for nephrologist consultation referral who are actually referred.
  5. Changes in blood pressure control rate: the difference in proportion of CKD patients achieving a target of <130/80 mmHg, based on available tests.
  6. Changes in glycemic control rate: the difference in the proportion of CKD patients achieving a HbA1c <7%, based on available tests.
  7. Changes in lipid control rate: the difference in the proportion of CKD patients achieving a LDL-C <2.6 mmol/L, based on available tests.
  8. Cost-effectiveness of the CKD-CDSS: economic evaluation of the community-based CKD screening and management program.
  9. CDSS implementation process: process evaluation using the RE-AIM framework (**Table 5**) to understand the implementation of this complex intervention. This evaluation examines the factors influencing outcomes across five dimensions—Reach, Effectiveness, Adoption, Implementation, and Maintenance—at both the individual and organizational levels. An initial phase, structured questionnaires for community institutions and physicians (**Table 6**) will be used to inform the timely optimization of the CDSS and its implementation strategy.

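### The CKD diagnosis-rate outcome is taken over a cohort partly selected on having a CKD code, which raises the reported baseline rate and dilutes the absolute effect on underdiagnosis by an unreported share

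*Protocol*

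**What the plan says.** Protocol 3.1.2.1 sets three alternative routes into the CKD cohort: "Diagnosis of CKD, defined as meeting at least one of the following criteria". Routes (1) and (2) are laboratory routes and ask for two abnormal findings at least 90 days apart: two low eGFR values, or "Confirmed proteinuria, defined as two positive results". Neither needs a code. Route (3) is code-based: "Documented CKD diagnostic codes in the EHR, supplemented by at least one qualifying eGFR or proteinuria result meeting the above thresholds". It needs only one abnormal result and gives no time window for the code.

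The objective (2.2.2, process measure 1) is: "To assess the effect of the CDSS on the underdiagnosis of CKD, as measured by the rate of appropriate ICD-coded documentation in patient records". The outcome (3.3.2, item 1) is: "the difference in the proportion of CKD patients with an ICD-code for CKD documentation between the follow-up and baseline periods". Its population is CKD patients without further restriction, so all three routes count.

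Baseline coding status comes from the screening period that also supplies the cohort. Section 3 says so of "Baseline characteristics, including CKD diagnosis (based on ICD codes") and the clinical measures. On the model, 3.6.2.1 says: "Other secondary outcomes will be analyzed using the same approach but without adjustment for baseline eGFR". The adjustment set is then age, sex and comorbidities. Neither entry route nor baseline coding is named.

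**The concern.** Whether a patient carries a CKD code is the outcome, and it is also one of the ways into the denominator. Patients who enter only through criterion (3) are coded by construction. They raise the baseline rate and, if their code stands, cannot become newly diagnosed. An uncoded patient with a single abnormal result is left out, while a coded patient with the same result is let in. That asymmetry pushes the coded proportion up as well.

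Two readings are at stake. The reported baseline level would look better than documentation really is among patients whose laboratory results establish CKD. The absolute change would be averaged over patients who have no room to change. The objective concerns underdiagnosis, and the patients who can show it are those with laboratory-defined CKD and no code.

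**Working it through.** The protocol states no baseline rate, effect size or power for this outcome, so there is no figure to reproduce. The check is algebra, followed by a range.

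**Inputs**
- From the protocol: the three entry routes (3.1.2.1), the outcome over all CKD patients (3.3.2), and baseline coding taken from the screening period (section 3).
- Assumed, because the protocol gives no value: q, the share of the cohort entering only by criterion (3), and b, the coded share at baseline among patients meeting criterion (1) or (2).
- Also assumed: criterion (3) codes count as baseline codes, and a code once recorded carries forward.

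**Baseline rate**
- Whole cohort = q × 1 + (1 − q) × b = b + q(1 − b).
- Inflation over the laboratory-defined rate b is therefore q(1 − b), which is above zero for any q > 0 and b < 1.

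**Absolute effect**
- If the between-arm effect is Δ in laboratory-defined patients and zero in criterion-(3)-only patients, the whole-cohort effect is q × 0 + (1 − q) × Δ = (1 − q)Δ.
- Relative to the effect among patients uncoded at baseline, the factor is (1 − q)(1 − b).

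**Results with b = 0.20 and, for illustration, Δ = 10 points**

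| q | Baseline rate, whole cohort (laboratory-defined: 20%) | Share of Δ kept | Whole-cohort difference | Share kept of the effect in uncoded patients |
|---|---|---|---|---|
| 0.1 | 0.1 + 0.9 × 0.2 = 28% | 90% | 9 points | 72% |
| 0.3 | 0.3 + 0.7 × 0.2 = 44% | 70% | 7 points | 56% |
| 0.5 | 0.5 + 0.5 × 0.2 = 60% | 50% | 5 points | 40% |
| 0.7 | 0.7 + 0.3 × 0.2 = 76% | 30% | 3 points | 24% |

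The other unknown matters for the level too. At q = 0.3 the whole-cohort baseline is 33.5% if b = 0.05 and 58% if b = 0.40.

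**Power**
- Scenario (assumed): 15 centres per arm, 108 patients per centre (3,240 / 30), ICC 0.02, half the cohort coded at baseline and staying coded, new coding 10% v 20% in the rest.
- Follow-up proportions only: 0.5 + 0.5 × 0.10 = 0.55 v 0.5 + 0.5 × 0.20 = 0.60. Power is about 35%, against 97% in uncoded patients alone (54 per centre).
- Change from baseline, which is what 3.3.2 defines: a patient who stays coded adds nothing to the change and nothing to its variance, so effect and standard error shrink together. Simulated with a centre-level t test and the coded share varying between centres, power is about 95% for the whole cohort and 97% for uncoded patients.

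The large power gap therefore belongs to a follow-up-only comparison and not to the outcome as defined.

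**The case against.** The strongest case on the other side has four parts.

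- **The outcome matches the words of the objective.** The objective is measured by a documentation rate in patient records, and a rate over all CKD patients is such a rate. Criterion (3) also has a legitimate purpose: a coded patient with a supporting result is reasonably part of the cohort for the hospitalisation endpoint. This stands as a reason to leave cohort entry alone. It does not rescue the denominator of outcome 1, because the same objective names underdiagnosis and code-entered patients cannot show it.
- **Carry-forward is not stated.** If coding is ascertained afresh in each period, a patient coded at baseline can be uncoded in follow-up, and an old code admitted by criterion (3) might not count at baseline. This stands. The algebra is then approximate, and the outcome would partly measure re-recording of known cases.
- **Both arms are treated alike.** The cohort comes from a fixed screening period under one rule for every centre. This stands: a reader might infer bias towards one arm, and the documents do not support that.
- **The size is unknown.** A reader might infer that most of the effect is hidden. That needs q above 0.5, or, measured against uncoded patients, a total coded share q + (1 − q)b above 0.5. The protocol gives neither figure, and its background premise of substantial underdiagnosis lends no support to a large coded share. At q = 0.1 to 0.3, 90% to 70% of the effect in laboratory-defined patients remains.

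A reader might also infer a severe loss of power. That follows only if the baseline term in 3.3.2 is dropped. How baseline enters the mixed model can properly be left to a statistical analysis plan.

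**Conclusion.** The point holds as one of attenuation and a misstated level. The denominator of secondary outcome 1 is selected on the outcome, and nothing elsewhere in the protocol restricts it to laboratory-defined or uncoded patients. The direction is certain for any q > 0 and b < 1 if codes carry forward. The amount depends on q and b, which the protocol does not report. With b = 0.20 assumed, q from 0.1 to 0.7 moves the baseline rate from 20% to between 28% and 76%, and leaves 90% to 30% of the absolute effect in laboratory-defined patients.

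The point concerns one secondary process outcome and leaves the primary endpoint untouched. It is still worth correcting in the protocol, because the population of the outcome is written there and the data for a better denominator are already collected.

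**What to change.** In 3.3.2, item 1:

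- Define the analysis population as patients meeting laboratory criterion (1) or (2) of 3.1.2.1 with no CKD code in the screening period. The event is the first CKD code during follow-up.
- Report the baseline documentation rate in all criterion (1)/(2) patients, coded or not, since it is zero by construction in the analysis population.
- Report descriptively the whole-cohort coded proportion at baseline and follow-up, and the share of the cohort that entered only by criterion (3).
- For the descriptive whole-cohort figure, state whether a baseline code carries forward or must be recorded again in follow-up.

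The cost is a few sentences. Cohort entry, data collection and the primary endpoint do not change. The downside is that the main result for this outcome no longer covers patients already coded, so persistence of documentation appears only in the descriptive figures.
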